#### **5. Participants**

The participants of this study are adults aged 18 and older who have been inoculated with 2 or 3 doses of inactivated COVID-19 vaccines  $\geq 6$  months.

#### **6. Study Design**

##### **6.1. Study objective(s)**

##### **6.1.1. Primary objective(s)**

---

➤ **The primary objective of protective efficacy**

1) To evaluate the protective efficacy of the investigational vaccine or placebo in the prevention of symptomatic COVID-19 cases of any severity (Appendix 1) occurring from 14 days after booster vaccination in adults aged 18 and older who have completed 2 or 3 doses of inactivated COVID-19 vaccines.

**6.1.2. Secondary objective(s)**

➤ Secondary objective(s) of protective efficacy

1) To observe the protective efficacy of the investigational vaccine or placebo in the prevention of severe and critical COVID-19 cases (Appendix 1) from 14 days after booster vaccination in adults aged 18 and older who have completed 2 or 3 doses of inactivated COVID-19 vaccines.

2) To observe the protective efficacy of the investigational vaccine or placebo in the prevention of COVID-19 cases leading to death (Appendix 1) from 14 days after booster vaccination in adults aged 18 and older who have completed 2 or 3 doses of inactivated COVID-19 vaccines.

➤ Secondary objective(s) of safety

1) To evaluate the safety of the investigational vaccine or placebo within 28 days after booster vaccination in adults aged 18 and older who have completed 2 or 3 doses of inactivated COVID-19 vaccines.

2) To observe the safety of the investigational vaccine or placebo within 6 months after booster vaccination in adults aged 18 and older who have completed 2 or 3 doses of inactivated COVID-19 vaccines.

➤ Secondary objective(s) of immunogenicity

---

1)To evaluate the SARS-CoV-2 virus-neutralizing antibody against the main epidemic strains among the immunogenicity subgroup 7 days, 14 days, 28 days, 3 months, and 6 months after booster vaccination of the investigational vaccine or placebo.

2)To evaluate the SARS-CoV-2 S-protein IgG antibody against the main epidemic strains among the immunogenicity subgroup 7 days, 14 days, 28 days, 3 months, and 6 months after booster vaccination of the investigational vaccine or placebo.

### **6.1.3. Exploratory objective(s)**

➤ Exploratory objective(s) of protective efficacy

1)To observe the protective efficacy of the investigational vaccine or placebo in the prevention of symptomatic COVID-19 cases of any severity (Appendix 1) occurring from 7 days after booster vaccination in adults aged 18 and older who have completed 2 or 3 doses of inactivated COVID-19 vaccines.

➤ Exploratory objective(s) of immunogenicity

1)To observe the specific cellular immune response among the immunogenicity subgroup 7 days, 14 days, 28 days, and 3 months after booster vaccination of the investigational vaccine or placebo in the adults aged 18 and older who have completed 2 or 3 doses of inactivated COVID-19 vaccines.

To explore the relationship between neutralizing antibody, S-protein IgG antibody, and/or cellular immunity and vaccine protective efficacy after vaccination.

## **6.2. Study endpoint(s)**

### **6.2.1. Primary endpoint(s)**

➤ The primary endpoint(s) of protective efficacy

1)The person-year incidence rate of symptomatic COVID-19 cases of any severity (Appendix 1) occurring from 14 days after booster vaccination of the investigational

---

vaccine or placebo in adults aged 18 and older who have completed 2 or 3 doses of inactivated COVID-19 vaccines.

#### **6.2.2. Secondary endpoint(s)**

➤ Secondary endpoint(s) of protective efficacy

1)The person-year incidence rate of severe and critical COVID-19 cases (Appendix 1) occurring from 14 days after booster vaccination of the investigational vaccine or placebo in the adults aged 18 and older who have completed 2 or 3 doses of inactivated COVID-19 vaccines.

2)The person-year incidence rate of COVID-19 cases leading to death (Appendix 1) occurring from 14 days after booster vaccination of the investigational vaccine or placebo in adults aged 18 and older who have completed 2 or 3 doses of inactivated COVID-19 vaccines.

➤ Secondary endpoint(s) of immunogenicity

1)The geometric mean titer (GMT), geometric mean increase (GMI), and seroconversion rate (SCR) of SARS-CoV-2 virus neutralizing antibody against the main epidemic strains among the immunogenicity subgroup 7 days, 14 days, 28 days, 3 months and 6 months after booster vaccination of the investigational vaccine or placebo.

2)The geometric mean titer (GMT), geometric mean increase (GMI), and seroconversion rate (SCR) of SARS-CoV-2 S-protein IgG antibody against the main epidemic strains among the immunogenicity subgroup 7 days, 14 days, 28 days, 3 months and 6 months after booster vaccination of the investigational vaccine or placebo.

➤ Secondary endpoint(s) of safety

---

1)The incidence of AEs within 30 mins, 14 days, and 28 days after booster vaccination of the investigational vaccine or placebo in adults aged 18 and older who have completed 2 or 3 doses of inactivated COVID-19 vaccines.

2)The incidence of SAEs and AESIs within 6 months after booster vaccination of the investigational vaccine or placebo in adults aged 18 and older who have completed 2 or 3 doses of inactivated COVID-19 vaccines.

3)The pregnancy events (including the pregnancy outcome, the delivery characteristics, the condition of the newborn, and the growth and development within 1 month after birth) within 6 months after booster vaccination of the investigational vaccine or placebo in the adults aged 18 and older who have completed 2 or 3 doses of inactivated COVID-19 vaccines.

### **6.2.3. Exploratory endpoint(s)**

➤ Exploratory endpoint(s) of protective efficacy

1)The person-year incidence rate of symptomatic COVID-19 cases of any severity (Appendix 1) occurring from 7 days after booster vaccination of the investigational vaccine or placebo in the adults aged 18 and older who have completed 2 or 3 doses of inactivated COVID-19 vaccines.

➤ Exploratory endpoint(s) of immunogenicity

1)The specific cellular immune response detected via cytokines IL-2, IL-4, IL-13, IFN- $\gamma$  (ELISpot) among the immunogenicity subgroup 7 days, 14 days, 28 days, and 3 months after booster vaccination of the investigational vaccine or placebo.

2)The correlation coefficient between neutralizing antibody, S-protein IgG antibody, and/or cellular immunity and vaccine protective efficacy after vaccination.

---

### **6.3. Overall Design**

A single-center, randomized, blinded, placebo-controlled design will be used for this study.

### **6.4. Study hypothesis**

The lower limit of the confidence interval for the protection efficacy (vaccine efficacy, VE) against symptomatic COVID-19 cases occurring from 14 days after booster vaccination in adults aged 18 and older is more than 30%.

Null hypothesis(H0): the lower limit of 95% confidence interval for the VE  $\leq 30\%$

Alternative hypothesis(H1): the lower limit of 95% confidence interval for the VE  $> 30\%$

The overall test level of the study is  $\alpha=0.025$ (one-sided).

### **6.5. Sample size and groups**

#### **6.5.1. Sample size estimation**

This study is a randomized, blinded, placebo-controlled clinical study. The sample size for this study is estimated as follows:

Sample size of protective efficacy: Assume that the incidence rate of COVID-19 in the study area will be approximately 9% and the expected VE of the vaccine will be at least 60%. The superiority margin of VE is 30%, the allocation ratio of the experimental group to the placebo control group is 1:1, the test level is 0.025 on one side, and the power of the test is 90%. The sample size is calculated using the exact conditional method under the large-sample Poisson distribution based on Chan and Bohidar. At least 162 confirmed cases of COVID-19 with clinical symptoms should be collected in the study, and a sample size of 1,286 participants is required for each

---

group. Considering about 20% non-evaluable rate, 1,600 participants are planned to be enrolled in each group, with a total of 3,200 participants.

Due to the unpredictability of the number of cases in some areas and the change in the incidence rate in different regions, the number of COVID-19 cases will be monitored blindly during the research. The number of participants planned to be enrolled can be increased during the study according to the changes of the incidence in different regions, but the required number of clinically symptomatic COVID-19 cases of any severity cannot be changed, thus not causing inflation of the overall Type I error of the study.

### 6.5.2. Sample Size Allocation

This study plans to enroll approximately 3,200 participants who have completed 2 or 3 doses of inactivated COVID-19 vaccine for  $\geq 6$  months (Study No. 0001~3200). All participants with informed consent, physical examination, and screening will be 1:1 randomly assigned into the experimental group or the control group (1,600 participants in each group) and followed up for safety and protective efficacy.

In this study, the first 50 participants enrolled in each group (a total of 100 participants) will be set as the immunogenicity subgroup (Study No. 0001~0100). All participants enrolled need to be followed up for safety and protective efficacy after vaccination. The participants in the immunogenicity subgroup also need to collect blood for the detection of immunogenicity-related indicators before vaccination and 7 days, 14 days, 28 days, 3 months, and 6 months after vaccination. Extra blood will be collected for cellular immunity test before vaccination and at days 7, 14, 28, and month 3 after vaccination.

The groups, vaccines, and planned sample size are detailed in the table below:

| Participants                           | Groups        | Vaccines | Immunogenicity subgroup | Non-immunogenicity subgroup | Sample size(no.) |
|----------------------------------------|---------------|----------|-------------------------|-----------------------------|------------------|
| Adults aged 18 and older who have been | Study group   | LVRNA012 | 50                      | 1550                        | 1,600            |
|                                        | Control group | Placebo  | 50                      | 1550                        | 1,600            |

---

|                                                                                                  |       |     |      |       |
|--------------------------------------------------------------------------------------------------|-------|-----|------|-------|
| inoculated with 2 or 3

doses of inactivated

COVID-19 vaccines for

≥6 months | Total | 100 | 3100 | 3,200 |
|--------------------------------------------------------------------------------------------------|-------|-----|------|-------|

## 6.6. Observation of protective efficacy

**7 days after the booster vaccination for every participant, the investigators need to carry out the following "routine monitoring" on the participants through a combination of remote visits and on-site visits:**

- The investigators remotely visit the participants to see if they have symptoms related to COVID-19;
- When the investigator learns that the participant has any one or more of the following conditions through remote visits, it is necessary to collect the participant's throat swab sample A1 (for SARS-CoV-2 nucleic acid or antigen detection), and further inquiry, record, and guidance should be done to the participant to continue to observe and record symptom types, start and end time, severity, etc. If an on-site visit is conducted to the participant (the on-site visit could be carried out by the participant going to the study site or the investigators' visit), another nucleic acid throat swab sample B1 (backup sample) needs to be collected:

④ *Any possible signs or symptoms related to COVID-19 appear (fever or chills, malaise/fatigue, headache, dry throat, muscle pain, sore throat, nasal congestion/runny nose, anorexia/nausea/vomiting, diarrhea, new sense of smell/dysgeusia, conjunctivitis);*

⑤ *Any one or more respiratory-related symptoms (cough, shortness of breath, or dyspnea) appear and last for any time;*

⑥ *Clinical or imaging evidence of pneumonia.*

**If the result of SARS-CoV-2 nucleic acid or antigen detection of the participant's throat swab sample A1 is positive, the investigators need to**

---

**continue to carry out the following "case monitoring" on the participant:**

- Send the participant's nucleic acid throat swab sample B1 (if collected) to the central laboratory for SARS-CoV-2 variant strain type detection, and guide the participant to go to the designated hospital for chest imaging examination (chest CT) ;
- Provide necessary medical supplies to the participant, and continue to remotely visit him/her twice a week. Instruct the participant to observe and record symptoms and self-medication at home, or guide him/her to go to the designated hospitals for medical treatment according to the situation. If the participant has symptoms such as shortness of breath or dyspnea, guide him/her to detect blood oxygen saturation according to the situation. According to the symptoms recovery of the participant, conduct an on-site visit to collect a throat swab sample or antigen nasopharyngeal swab sample for SARS-CoV-2 nucleic acid or antigen detection, until the result of SARS-CoV-2 nucleic acid or antigen turns negative or the symptoms disappear or stabilize under the investigators' evaluation.
- Collect the participant's treatment and medical history to judge the severity of COVID-19, and make the records about the type, starting time, and reporting time of the participant's symptom, and the collection time, detection time, and reporting time of each nucleic acid sample, and the diagnosis time and outcome of the case, to form relevant records;
- Establish a COVID-19 case file for the participant, and fill in and report the first/follow-up COVID-19 case report according to the remote visit;
- On-site monitoring and medical monitoring teams need to conduct a preliminary review of the completeness, rationality, and logic of the COVID-19 case report, and raise necessary inquiries and requirements of information supplementary, then submit them to the investigators for diagnosis and judgment.

**If the result of SARS-CoV-2 nucleic acid or antigen detection in the participant's throat swab sample A1 is negative, the following retest should be continued:**

- 
- The participant's throat swab sample A2 (for SARS-CoV-2 nucleic acid or antigen detection) and sample B2 (backup sample) need to be collected again within 48 hours;
  - If the result of SARS-CoV-2 nucleic acid or antigen detection of the participant's throat swab sample A2 is positive, the above "case monitoring" process should be followed to carry out relevant work;
  - If the result of SARS-CoV-2 nucleic acid or antigen detection of the participant's throat swab sample A2 is still negative, the above "routine monitoring" process should be continued to carry out relevant work.

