### **11.3.2. Case surveillance**

**If the test result for SARS-CoV-2 nucleic acid or antigen in the throat swab sample A1 of the subject is positive, the researcher needs to continue to carry out the following "case monitoring" work:**

- Send the throat swab sample B1 of the subject's nucleic acid (if collected) to the central laboratory for SARS-CoV-2 variant typing testing, guide and coordinate the subject to go to a designated hospital for chest imaging examination (chest CT);
- Provide necessary medical supplies to the subjects, continue to conduct remote visits twice a week, guide them to observe and record symptoms and self-medication at home, or guide them to seek medical treatment at designated hospitals according to the situation; If the subject has symptoms such as Tachypnea or dyspnea, guide and coordinate the subject to detect blood oxygen saturation according to the situation; According to the recovery of symptoms of the subjects, conduct on-site visits, collect samples of nucleic acid oropharyngeal swabs or antigen Nasopharyngeal swab for SARS-CoV-2 nucleic acid or antigen detection until the results of SARS-CoV-2 nucleic acid or antigen turn negative

---

or the symptoms disappear or stabilize according to the evaluation of the investigator;

- Collect the treatment status and medical history of the subjects to determine the severity of COVID-19, record the type of symptoms, occurrence time, reporting time, collection time, testing time, reporting time, diagnosis time, and outcome information of each nucleic acid sample, and form relevant records;
- Establish a COVID-19 case file for the subjects, fill out and report the first/follow-up COVID-19 case report based on remote visits;
- The on-site and medical monitoring teams need to conduct a preliminary review of the completeness, rationality, and logic of the COVID-19 case report, raise necessary questions and information supplement requirements, and submit it to the researchers for diagnosis and judgment.

**If the test result of the throat swab sample A1 for SARS-CoV-2 nucleic acid or antigen is negative, the following retesting work needs to be continued:**

- Within 48 hours, the throat swab sample A2 (for SARS-CoV-2 nucleic acid or antigen testing) and sample B2 (backup sample) need to be collected again;

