- If the test result for SARS-CoV-2 nucleic acid or antigen in the throat swab sample A2 of the subject is positive, the relevant work shall be carried out according to the above case monitoring process;
- If the test result for SARS-CoV-2 nucleic acid or antigen in the throat swab sample A2 of the subject is still negative, the relevant work will continue according to the routine monitoring process mentioned above.

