#### **11.8.2.3. Protection effectiveness analysis**

The person-year incidence rates and 95% confidence interval(CI) of COVID-19 confirmed by the central laboratory with clinical symptoms will be calculated among the test group and the control group 14 days after the vaccination, and the Poisson regression model will be used to analyze the statistical differences between the groups. VE and 95% CI based on the person-year incidence rates will be estimated with the model. The Poisson regression model takes the number of patients as the dependent variable, grouping as the fixed effect, and the exposure person-years of the participants as the offset, using the log connection function.

Person-year incidence rate=(number of cases)/(exposure person-years of the participants)×100%. In the calculation of the exposure person-years, the starting time is the 14th day after the vaccination, and the ending time is the day when a COVID-19 case was first confirmed. If the RT-PCR or antigen test was positive but not confirmed as a COVID-19 case, the person-year incidence rate was calculated using the RT-PCR or antigen test date as the termination time. VE rate=1- (person-year incidence rate of the test group)/(person-year incidence rate of the control group).

---

The VE will be evaluated in the prevention of clinically symptomatic COVID-19 confirmed by central laboratory virology 14 days after vaccination based on the sets of E-mFAS and E-PPS. The evaluation of VE based on E-mFAS is the main analysis result of this study.

In addition, the VE of the vaccine against clinically symptomatic COVID-19 confirmed by central laboratory virology 7 days after vaccination will be evaluated based on E-mFAS, and the statistical method is the same as the primary efficacy endpoint.

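### For cases found only on the retest, the case-monitoring procedure names the backup swab taken with the negative test (B1) for central typing and gives the swab taken with the positive test (B2) no use

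*Protocol*

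**What the plan says.** Section 6.6 and the matching synopsis text set out two pairs of swabs.

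- **First contact.** A symptomatic participant gives A1, tested by nucleic acid or antigen. Only if there is an on-site visit does the rule add that "another nucleic acid throat swab sample B1 (backup sample) needs to be collected".
- **A1 positive.** Case monitoring starts. Its shipping step is "Send the participant's nucleic acid throat swab sample B1 (if collected) to the central laboratory for SARS-CoV-2 variant strain type detection". Section 11.3.2 repeats it: "Send the throat swab sample B1 of the subject's nucleic acid (if collected) to the central laboratory for SARS-CoV-2 variant typing testing".
- **A1 negative.** A second swab A2 is taken, and "sample B2 (backup sample) need to be collected again within 48 hours". This step is not made conditional on an on-site visit.
- **A2 positive.** Section 11.3.2 says that if "throat swab sample A2 of the subject is positive, the relevant work shall be carried out according to the above case monitoring process". The synopsis and 6.6 say the same in slightly different words. None of the three names a different sample to ship.

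Two other places bear on the consequence. Section 11.8.2.3 describes the primary analysis as counting COVID-19 "confirmed by the central laboratory with clinical symptoms". Appendix 1 defines a primary case by symptoms (or evidence of pneumonia) plus a positive nucleic acid or antigen test, and does not mention a central laboratory.

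**The concern.** The instruction for A2-positive cases borrows a procedure written for A1-positive cases and does not adapt the sample label. The labels are not interchangeable: the protocol numbers the backups separately, and B1 and B2 can be up to 48 hours apart.

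The direct stake is strain typing, which is the stated purpose of the shipment. Section 3.2.1 describes BF.7, BQ.1, BQ.1.1 and XBB displacing BA.5.2 in some places, so strain data matter when interpreting the efficacy of a BA.5 vaccine. A swab paired with a negative test is a poorer candidate for typing than one paired with a positive test.

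The second stake is conditional. B1 is the only respiratory sample that the monitoring procedure expressly sends to the central laboratory. If 11.8.2.3 is applied as worded, the central result for an A2-positive case would have to come from B1 or would not exist. Section 11.8.2.3 also ends exposure time at the test date when a positive test is not confirmed as a case, so such a person would leave the numerator and be censored there.

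**Working it through.** **Step 1: trace each path.** The inputs are the collection and shipping rules in 6.6 and 11.3.2.

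| Path | Swabs on hand | Shipped as written | Paired test |
|---|---|---|---|
| A1 positive, on-site first contact | A1, B1 | B1 | positive A1 |
| A1 positive, no on-site visit | A1 | none | – |
| A1 negative, A2 positive, on-site first contact | A1, B1, A2, B2 | B1 | negative A1 |
| A1 negative, A2 positive, no on-site first contact | A1, A2, B2 | none | – |

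The last two rows are the point. In both, B2 exists and is paired with the positive test, yet no sentence ships, types or tests it. B2 appears only where it is collected, in the synopsis, 6.6 and 11.3.2, so no section corrects another.

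**Step 2: does this reach the primary endpoint?**
- Under Appendix 1, a symptomatic participant with a positive A2 is a case. No central result is needed, so only typing is affected.
- Under 11.8.2.3 as worded, central confirmation is part of what is counted. A retest-detected case then depends on B1, or has nothing to depend on.

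The consequence for the primary count therefore turns on which text governs, and the protocol does not settle that.

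**Step 3: size.** The protocol gives no share of cases that are A1-negative and A2-positive, so no number affected can be derived. The following is illustration only.

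- The plan's own figure reproduces: with 9% incidence and VE 60%, the mean case count per participant pair is 0.09 × (1 + 0.4) = 0.126, and 162 / 0.126 = 1,286 per group.
- Exact conditional test: p0 = 0.7/1.7 = 0.412, p1 = 0.4/1.4 = 0.286, one-sided 0.025. At 162 cases the attained level is 0.0247 and power is 92.2%.
- Assume that 5%, 10% or 20% of 162 cases were found only on A2: 8, 16 or 32 cases. If every one were lost and none replaced, 154, 146 or 130 would remain, with power 90.8%, 89.2% or 85.1%.
- Exact power moves unevenly with the case count (159 cases also give 89.2%), so small differences here mean little.

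These figures need four things at once: the assumed share, 11.8.2.3 overriding Appendix 1, failure of every affected case, and no replacement. The last conflicts with the design. Section 6.5.1 fixes the required number of cases and allows enrolment to rise, and 6.6 keeps twice-weekly visits going after day 90 until 162 confirmed cases are reached.

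**Step 4: bias.** If the same fraction k of cases is retained in each arm, VE = 1 − (k × rate in vaccine arm)/(k × rate in placebo arm), and k cancels. Exposure time ends at the positive test or the confirmed case either way, so it is nearly unchanged. Nothing in the protocol indicates that k differs between arms.

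**The case against.** The strongest reply is that staff would read the reference to case monitoring sensibly. The labels A1/B1 and A2/B2 run in parallel, B2 is called a backup, and nothing forbids sending it. This reading is reasonable, and the defect is best described as a cross-reference that was not adapted. But reaching the sensible action means overriding a sample that the text names explicitly, in three places.

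A reader might infer that these cases are confirmed on the wrong sample. The documents do not support that. The shipping step is for variant typing, and Appendix 1 accepts the positive A2. Confirmation is touched only through the separate conflict between 11.8.2.3 and Appendix 1, which affects A1-positive cases too.

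A reader might also infer that every retest-detected case is typed on a swab paired with a negative test. That goes too far: B1 exists only after an on-site first contact, and otherwise nothing is sent. Nor does a negative A1 prove that B1 is negative. A1 may be an antigen test, whereas B1 is a nucleic acid swab.

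Finally, no objective or endpoint in 6.1 or 6.2 is variant-specific, so a loss confined to typing changes no listed endpoint. This stands, and it limits the weight of the point.

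**Conclusion.** The routing defect is established from the text alone. For A1-negative, A2-positive cases, the procedure as written offers the central laboratory the backup paired with the negative test, or none, and leaves the backup paired with the positive test without a use.

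The certain consequence, if the text is followed literally, is weaker or missing strain typing for these cases. A consequence for the primary count is possible only if the central-confirmation wording in 11.8.2.3 is applied over Appendix 1.

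The number of such cases is unknown. A reader might infer lost cases and reduced power, but neither is shown: the design collects to 162 confirmed cases, so under a central-confirmation rule the expected effect is longer collection or more enrolment. Bias in VE is not shown either, and 6.11.6 keeps efficacy observers and laboratory staff blinded. The point is modest, but the rule is misstated and should be corrected.

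**What to change.** In the synopsis, 6.6 and 11.3.2, replace *sample B1 (if collected)* in the shipping step with *the backup sample taken with the positive swab (B1 if A1 is positive, B2 if A2 is positive)*. Keep a qualifier for the case where no B1 was taken with a positive A1.

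The cost is one phrase in three places and a matching line in any site or laboratory instructions. No extra swab or visit is needed, because B2 is already collected; the shipments and typing tests are those that the procedure already intends for a positive case.

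Whether a primary case needs central confirmation (11.8.2.3) or only a positive nucleic acid or antigen test (Appendix 1) is a separate matter to reconcile. Correcting the routing does not settle it, but supplies the appropriate retest swab under either answer.
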